# Efficacy and cerebral mechanisms of acupuncture for chronic obstructive pulmonary disease: study protocol for a multicenter, randomized controlled neuroimaging trial

**DOI:** 10.3389/fneur.2024.1363225

**Published:** 2024-06-26

**Keywords:** dyspnea, chronic obstructive pulmonary disease, acupuncture, functional magnetic resonance imaging, randomized controlled trial, protocol

## Abstract

**Introduction:**

Although acupuncture is recommended by chronic obstructive pulmonary disease (COPD) treatment guidelines owing to its effects on dyspnea, the underlying neurobiological mechanisms of these effects remain unclear. This study aims to evaluate the efficacy of acupuncture in patients with stable COPD and explore the possible involvement of specific brain regions.

**Methods:**

This is a prospective, multicenter, single-blind, randomized controlled trial. A total of 90 participants will be recruited from three centers and will be randomly assigned in a 1:1 ratio to undergo acupuncture at acupoints on the disease-affected meridian (DAM) or non-acupoints on the non-affected meridian (NAM), in addition to routine pharmacological treatments. All participants will undergo 30 min of acupuncture three times a week for 8 weeks and will be followed up for 12 months. The primary outcome will be the severity of dyspnea, as measured using the Borg Dyspnea Scale and a visual analog scale at rest and after exercise. The secondary outcomes will include the multidimensional profile of dyspnea using Dyspnea-12, the modified Medical Research Council Dyspnea Scale, and the COPD assessment test; quality of life assessments using St George's Respiratory Questionnaire and the Hospital Anxiety and Depression Scale; and additional measurements of exacerbation frequency, pulmonary function, and the 6-min walking distance. Magnetic resonance imaging (MRI) will be performed before and after exercise to explore the potential neurobiological mechanisms of exertional dyspnea. Anxiety and depression will be measured and analyzed for their correlation with the activation of specific brain areas involved in dyspnea.

**Discussion:**

This randomized controlled trial aims to use a multidimensional evaluation of the efficacy of acupuncture in relieving dyspnea in patients with COPD in terms of emotion and quality of life and explore the neurobiological mechanisms underlying the effects of acupuncture on dyspnea from an imaging perspective. It is expected to provide strong evidence to support the use of acupuncture in relieving dyspnea in patients with COPD and those with aother diseases involving dyspnea. Additionally, it provides novel insights into the central mechanisms of acupuncture intervention and dyspnea.

**Trial registration:**

Chinese Clinical Trial Registry (https://www.chictr.org.cn/): ChiCTR2300071725.

## 1 Introduction

Chronic obstructive pulmonary disease (COPD), a heterogeneous lung condition characterized by respiratory abnormalities and chronic respiratory symptoms including dyspnea, cough, or sputum, has a global prevalence of 10.1% and is the third leading cause of death worldwide (1–3). As one of the most common symptoms experienced by patients with COPD, dyspnea refers to a subjective experience of breathing discomfort that limits the abilities of patients to perform daily activities, resulting in anxiety and depression, which ultimately impacts the patients' quality of life (4–7). It is also an independent risk factor for COPD exacerbation and is associated with increased mortality (8, 9). Pharmacological therapies recommended by the 2023 Global Initiative for Chronic Obstructive Lung Disease for dyspnea relief include bronchodilators and methylxanthines; however, these therapies fail to rectify refractory breathlessness in patients with advanced disease, which may even result in adverse events such as arrhythmia or exacerbation (10–12). Complementary therapy is required for these patients. Acupuncture has been recommended by the Global Initiative for Chronic Obstructive Lung Disease as a non-pharmacological therapy since 2021 (13). A recent meta-analysis revealed that acupuncture may improve breathlessness and quality of life in patients with advanced COPD (14). However, the effect of acupuncture is still controversial, and the potential mechanism of acupuncture employed for relieving dyspnea in patients with COPD is still unclear.

As is well known, dyspnea is a multidimensional subjective experience that is influenced by emotions such as anxiety and depression (4). An increasing number of imaging studies suggest that it may be related to brain responses. Functional neuroimaging has shown that respiratory control and perception are modulated by the corticolimbic system of the brain (4, 15). Breathlessness in healthy individuals, as induced by lower tidal volume, inhaled CO_2_, and respiratory occlusions, is related to the activation of brain regions within the anterior insula (AI), which means that various neuronal networks may respond to dyspnea perception (16–18). Compared with healthy controls, patients with COPD exhibit increased neural respiratory drive and decreased gray matter, especially in the anterior cingulate cortex (ACC). These changes are related to disease severity and anticipatory fear of dyspnea and physical activity (19–21). Activation of the medial prefrontal cortex and ACC in COPD patients correlated with the subjective dyspnea (22). The ACC may be the core brain mechanism responsible for dyspnea. Interestingly, it could also be the neural mechanism involved in acupuncture. Studies on humans and animals have revealed that acupuncture exerts multiple beneficial effects on patients with various diseases through its impact on the central nervous system, as evidenced by hemodynamic indicators in the brain (23, 24). Acupuncture can enhance brain network connectivity within the ACC, amygdala, hippocampal formation, and cerebellum, i.e., the default mode network (DMN) and sensorimotor network, to modulate emotion, memory, perception, antinociceptive activity, and sensorimotor functions (23–26). Acupuncture exhibits an additive effect in patients with depressive disorder by increasing functional connectivity in the amygdala and the ACC (27). Breathlessness is typically accompanied by anxiety; anxiety sensitivity is positively correlated with AI activity and affects the Bayesian sensory perception system associated with breathlessness (28). Therefore, acupuncture, dyspnea, and anxiety may involve similar mechanisms in the central nervous system of patients with COPD. The change in the ACC may be the neural mechanism of acupuncture for treating dyspnea in patients with COPD, with emotion also playing a role in the acupuncture treatment process for dyspnea.

**Figure 1 F1:**
[figure not shown]
Study Hypotheses. The solid lines represent confirmed associations. The gray question mark indicates that the clinical efficacy of acupuncture in chronic obstructive pulmonary disease (COPD) still needs higher-quality clinical evidence; the blue question mark indicates that the neural mechanism of acupuncture for relieving dyspnea is still unknown; the red question mark indicates that the neural mechanism of acupuncture to relieve emotion affect is unknown, and its neural mechanism may overlap with dyspnea. The question mark indicates that the neural mechanism of exertional dyspnea induced by the 6-min walking test (6MWT) is unknown.

## 2 Methods and analysis

### 2.1 Study design

This is a prospective, multicenter, randomized, single-blind trial with two parallel groups involving patients with stable COPD. As shown in Figure 2, sociodemographic data will be collected, and participants will complete symptom questionnaires and undergo magnetic resonance imaging (MRI) before and after the 8-week intervention period. Patients will be followed up for 12 months via telephone interviews to perform COPD assessment test (CAT) and record COPD exacerbations. The exact timing of each outcome measurement is presented in Table 1.

**Figure 2 F2:**
[figure not shown]
Study flowchart.

**Table 1 T1:** Study schedule.

**Measurements**	**Screening visit**	**Visit 1 baseline**	**Visit 2 8 weeks**	**Phone interview 6 months**	**Phone interview 9 months**	**Phone interview 12 months**
Demographics, smoking history, and medical and treatment history	×	×				
Spirometry		×	×			
Dyspnea (Borg dyspnea scale and VAS)		×	×			
Dyspnea-12		×	×			
mMRC	×	×	×			
CAT		×	×	×	×	×
SGRQ		×	×			
6MWT		×	×			
Exacerbation		×	×	×	×	×
HADS		×	×			
MRI		×	×			

VAS, visual analog scale; mMRC, Modified Medical Research Council Dyspnea Scale; CAT, chronic obstructive pulmonary disease (COPD) assessment test; SGRQ, St George's Respiratory Questionnaire; 6MWT, 6-min walking test; HADS, Hospital Anxiety and Depression Scale; MRI, magnetic resonance imaging.

### 2.2 Participants

#### 2.2.1 Eligibility and recruitment

Patients will be enrolled from the West China Hospital, Sichuan University; the No. 3 Affiliated Hospital of Chengdu University of Traditional Chinese Medicine (West District)/Chengdu Pidu District Hospital of Traditional Chinese Medicine; and the Chengdu University of Traditional Chinese Medicine Affiliated Hospital, in Chengdu, China. Patients diagnosed with COPD will be contacted via phone to assess their basic eligibility and willingness to participate. Interested individuals will be scheduled for screening interviews. Individuals who meet the eligibility criteria will be informed about the study details and will be asked to sign an informed consent form. COPD will be diagnosed in accordance with the 2023 Global Initiative for Chronic Obstructive Lung Disease report (7).

#### 2.2.2 Inclusion criteria

The inclusion criteria are as follows: (1) diagnosis of COPD with clinically stable symptoms and no antibiotic or corticosteroid use, emergency room visits, or any hospitalizations due to COPD exacerbation in the preceding 4 weeks; (2) moderate-to-very severe airflow obstruction, defined as the post-bronchodilator forced expiratory volume in 1 s being < 80% predicted; (3) aged 40–80 years without limitation of sex; (4) ability to walk unaided; (5) no pulmonary rehabilitation in the preceding 6 months; and (6) willing to cooperate with the study and provide written informed consent.

#### 2.2.3 Exclusion criteria

The exclusion criteria are as follows: (1) presence of severe comorbidities such as various organ dysfunctions, chronic kidney disease, and malignancy; (2) presence of other chronic lung diseases such as asthma and bronchiectasis; (3) requirement for mechanical ventilation or oxygen therapy for more than 16 h/day; (4) uncontrolled hypertension or diabetes; (5) neurological diseases or limited mobility that may affect communication and walking; (6) pregnant or breastfeeding; (7) claustrophobia or other contraindications to MRI; and (8) participation in other clinical trials within the last 6 months or at the same time.

#### 2.2.4 Withdrawal criteria

During the intervention period, enrolled participants will be withdrawn from the study if they (1) experience serious adverse reactions or unexpected events that prevent continuing participation; (2) experience serious complications or a deterioration in their condition requiring urgent treatment; (3) express a request to withdraw from the clinical trial; or (4) express the intent that do not want to complete the planned treatment.

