### 2.6 Outcome measurement

All outcomes will be measured at baseline and after 8 weeks of intervention treatment.

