#### 2.6.1 Primary outcomes

The primary outcome is the severity of dyspnea measured after the 6-min walking test (6MWT). The severity of dyspnea at rest and exertional dyspnea after 6MWT will be assessed using the Borg Dyspnea Scale and a VAS, which are convenient, simple to use, and often used for measuring exertional dyspnea; scores will be recorded within 1 min of finishing the 6MWT.

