### 2.8 Statistical analysis

Qualitative variables will be expressed as numbers (percentages), and quantitative variables will be expressed as mean (standard deviation) or median (interquartile range [25%−75%], q1–q3). All efficacy evaluation data will be summarized according to the full analysis set and the per-protocol set. For safety analysis, the safety set will include all randomized participants who received at least one interventional treatment. A paired *t*-test or Wilcoxon signed-rank test will be conducted to compare the outcomes at baseline with those after the 8-week intervention period and during follow-up within a group. Analysis of covariance will be performed to compare the results after acupuncture and during follow-up between the groups. Exercise intensity will be adjusted to assess post-exercise dyspnea. Data will be analyzed using SPSS software version 26.0 (IBM Corporation, Armonk, NY, USA), and statistical significance will be set as a *p*-value of < 0.05.

Metadata from DICOM files will be converted to BIDS using HeuDiConv. fMRIPrep software version 21.0.4, a combination of tools from common software packages including FSL, ANTs, FreeSurfer, and AFNI, was developed by the laboratory of Russ Poldrack and the Stanford Center for Reproducible Neuroscience and will be used to perform minimal data preprocessing, including skull stripping, motion correction, segmentation, co-registration, and normalization. Motion artifacts will be removed automatically using independent component analysis (40). Subsequently, graph theory-based or data-driven approaches will be used to compare the differences between the DAM and NAM groups.

PANDA, a MATLAB toolbox that can be downloaded from https://www.nitrc.org/projects/panda/ and is based on MATLAB R2016a in the Ubuntu 16.04 operating system, will be used to analyze brain diffusion images. The coupling value between the functional connection matrix and the structural joint matrix will be calculated and correlated with clinical symptoms.

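### Section 2.2.4 treats stopping acupuncture as leaving the study, so week-8 and later outcomes would go uncollected for reasons tied to outcome or adherence

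*Protocol article*

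**What the plan says.** Section 2.2.4 of the protocol article opens with "During the intervention period, enrolled participants will be withdrawn from the study if they" and lists four criteria. The second is "2) experience serious complications or a deterioration in their condition requiring urgent treatment". The fourth is "4) express the intent that do not want to complete the planned treatment". A participant's own request to leave the trial is the third criterion, listed separately.

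On outcomes, section 2.6 states "All outcomes will be measured at baseline and after 8 weeks of intervention treatment". Section 2.6.1 makes dyspnea after the 6MWT primary, and Table 1 schedules Borg and VAS at baseline and Visit 2 (8 weeks) only. Section 2.1 adds "Patients will be followed up for 12 months via telephone interviews to perform COPD assessment test (CAT) and record COPD exacerbations", and Table 1 places the calls at 6, 9 and 12 months. The abstract lists exacerbation frequency among the secondary outcomes.

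On analysis, section 2.8 states "All efficacy evaluation data will be summarized according to the full analysis set and the per-protocol set". It defines neither set.

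**The concern.** Two different events are merged: ending the needling, and ending participation. Criteria 2 and 4 describe the first but trigger the second, for people who have not asked to leave. Nothing in the article arranges a Visit 2 assessment or telephone calls for them.

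Two consequences follow if sites apply the text as written.

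- The primary outcome has a single post-baseline time point. A participant withdrawn before week 8 has no primary value after baseline, and the reason for its absence is deterioration or poor adherence.
- Section 2.2.2 itself associates COPD exacerbation with emergency visits and hospitalization. An exacerbation in weeks 0–8 that needs urgent treatment is therefore both an outcome event and a reason to end the follow-up that counts exacerbations.

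The comparison of acupuncture on the disease-affected meridian (DAM) with the non-affected meridian control (NAM) would then rest on participants selected partly by how they fared. The allowance for dropout in section 2.4 protects precision. It does not protect comparability.

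**Working it through.** **The plan's own figure.** The only number in the article that bears on losses is the dropout allowance in section 2.4: 78 evaluable, 15% dropout, 45 per group. Multiplying gives 78 × 1.15 = 89.7, so 90, or 45 per group, which matches. Dividing gives 78 / 0.85 = 91.8, so 92, a difference of two patients. The point does not rest on this figure.

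**Exacerbations: inputs.** From the article: 8 weeks of intervention, 12 months of follow-up, 45 per arm. Assumed, because the article gives none: control rate r = 1.2 per year, true rate ratio 0.60 (so 0.72 per year on DAM), negative binomial counts with dispersion 1, and a fraction f of exacerbations that are urgent. Follow-up is taken as 52 weeks from the start of treatment, with T = 8/52 = 0.154 year.

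**Formulas.**
- Fraction withdrawn = 1 − 1/(1 + f·r·T)
- Mean 12-month count among those retained = [44/52 + (1 − f)·8/52] / (1/r + f·T)

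**Worst case, f = 1, withdrawn patients contributing nothing.**
- Control: withdrawn 1 − 1/(1 + 1.2 × 0.154) = 0.156. Retained mean 0.846/(0.833 + 0.154) = 0.86, against a true 1.20 (29% low).
- DAM: withdrawn 1 − 1/(1 + 0.72 × 0.154) = 0.100. Retained mean 0.846/(1.389 + 0.154) = 0.55, against a true 0.72.
- Apparent rate ratio: 0.548/0.857 = 0.64, against a true 0.60.

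**When only some exacerbations are urgent (same other assumptions).**

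| Urgent fraction f | Withdrawn, control v DAM | Retained control mean | Apparent ratio |
|---|---|---|---|
| 1 | 15.6% v 10.0% | 0.86 (29% low) | 0.64 |
| 1/2 | 8.5% v 5.2% | 1.01 (15% low) | 0.62 |
| 1/3 | 5.8% v 3.6% | 1.07 (11% low) | 0.61 |

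In the last row, 5.8% v 3.6% of 45 is 2.6 v 1.6 patients.

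**Other base rates.** With f = 1 and 0.5, 1.0, 1.5 or 2.0 exacerbations per year, the withdrawn fraction is 7%, 13%, 19% or 24%. These are upper limits for criterion 2, because not every exacerbation needs urgent treatment.

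**If the triggering event is counted but later ones are lost.** A simulation with control rates of 0.6 or 1.0 per year, all exacerbations urgent, a true ratio of 0.70 and gamma frailty of shape 1 or 0.5 gives an apparent ratio in mean counts of 0.73 to 0.77. Among completers only it is 0.72 to 0.75.

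**Primary outcome, illustration only.** If withdrawn patients would have scored m cm worse on the VAS than those retained, the retained comparison is shifted by (p_NAM − p_DAM) × m, where p is the proportion withdrawn. A 10-point difference in withdrawal with m = 1 to 3 cm gives 0.10 × 1 = 0.1 cm to 0.10 × 3 = 0.3 cm. Equal withdrawal with the same m gives no shift. No figure in the article fixes p or m.

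**The case against.** The strongest reply has four parts.

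- **The loss is inferred.** The article nowhere states that data collection stops at withdrawal, and it condenses a fuller protocol that may provide for follow-up. This stands as a limit on certainty. The published rule still says these participants leave the study, and nothing published qualifies it.
- **The exacerbation problem is narrow.** A reader might infer that the exacerbation endpoint as a whole censors itself. The text does not support that. The rule acts only in the intervention period, about 8 of 52 weeks, and only on deteriorations needing urgent treatment. Later or milder exacerbations trigger nothing. The triggering event may also be captured, since section 2.9 requires serious adverse events to be recorded. With its date kept, a rate analysis using time at risk could make use of it.
- **The figures are worst case and concern a secondary outcome.** This is correct. They rest on assumed rates, and the difference between arms arises only if treatment affects exacerbations from the start. With no such effect, this mechanism produces no difference between arms.
- **Collecting the data cures only part of it.** The primary value needs a 6MWT, which a recently deteriorated patient may be unable to do, and sensitivity analyses can bound the effect of missing values. Both are true. Questionnaires and calls remain obtainable, and for criterion 4 there is no evident reason why the 6MWT could not be done.

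A reader might also infer that the full analysis set is in effect a set of completers. Section 2.8 does not define that set, and its membership and the handling of missing values may properly sit in an analysis plan that is not shown. The point here concerns data collection and does not depend on that definition.

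**Conclusion.** The concern holds in limited form. Section 2.2.4 conflates stopping treatment with leaving the study. Followed as written, it removes the only post-baseline primary value and the later CAT and exacerbation calls for participants selected by deterioration or non-adherence. No definition of an analysis set restores values that were never collected.

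The size and direction of the bias depend on how withdrawals differ between arms, which the article does not allow anyone to estimate. Under the stated worst-case assumptions a true rate ratio of 0.60 reads 0.64, a modest shift toward no effect, and it shrinks to 0.62 or 0.61 if one half or one third of exacerbations are urgent. The effect on the primary outcome can only be illustrated, and criterion 4 is not quantified at all. This is a point that should be fixed. It does not show that the trial's primary comparison is invalid.

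**What to change.** Leave unchanged when treatment stops, and split section 2.2.4 in two.

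- **(a) Discontinuation of acupuncture, for whatever reason.** The participant stays in the study. The Visit 2 assessments already scheduled continue: 6MWT and post-6MWT dyspnea if the patient is able, questionnaires otherwise. The 6-, 9- and 12-month calls also continue.
- **(b) Withdrawal of consent for data.** This alone ends collection.

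Record the reason and date of each. Analyse randomised participants in their allocated arm using all data collected.

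The cost is an amendment to protocol and consent form at the three ethics committees named in the ethics statement, possibly with renewed consent for participants already enrolled. Visits and calls already planned are kept for some additional patients. Including partially treated patients dilutes the contrast slightly, and some post-6MWT values will still be missing.

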### 2.3 Randomization and blinding

Participants will be assigned in a ratio of 1:1 to undergo acupuncture at acupoints on the disease-affected meridian (DAM) or at non-acupoints on the non-affected meridian (NAM). The randomization sequence will be strictly executed according to the random number table generated by a third party; the randomization list will be blinded to other researchers or patients. Acupuncturists will be informed of the grouping to allow correct needle placement.

### 2.4 Sample size

The sample size calculation was based on the dyspnea visual analog scale (VAS) score, as reported by Liu et al. (29). The test for paired means in PASS software version 15.0.5 (NCSS Statistical Software, Kaysville, UT, USA) was used to calculate the dyspnea VAS score differences in the placebo and acupuncture groups before and after acupuncture, which determined that a total of 78 patients with stable COPD should be included in the study to achieve a statistical power of 0.95 and a significance level of 5% for difference detection. Assuming a dropout rate of 15% established the necessity of a sample size of 45 participants per group. The sample size calculation based on the Borg Dyspnea Scale, as reported by Li et al. (30), showed that a total of 16 patients with stable COPD should be included in the study to achieve a statistical power of 0.97 and a significance level of 5% for difference detection. Assuming a dropout rate of 20%, a sample size of 10 participants per group is required. This study, being a multicenter, clinical, randomized controlled trial, requires a larger sample size. Therefore, a sample size of 90 participants is considered to be reasonable for this study.

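### The stated power of 0.95 comes from a paired before-after test and is not shown to be the power of the randomised DAM versus NAM comparison

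*Protocol article*

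**What the plan says.** Section 2.4 of the protocol article starts from VAS results in a cited study. It names the method as "The test for paired means in PASS software version 15.0.5", which "was used to calculate the dyspnea VAS score differences in the placebo and acupuncture groups before and after acupuncture". The result is that "a total of 78 patients with stable COPD should be included in the study to achieve a statistical power of 0.95", with "a significance level of 5% for difference detection". The allowance for losses follows: "Assuming a dropout rate of 15% established the necessity of a sample size of 45 participants per group". The mean difference, SD, correlation and sidedness are not given.

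A second calculation, on the Borg scale, reports that "a total of 16 patients with stable COPD should be included in the study to achieve a statistical power of 0.97". It names no test.

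Section 2.3 allocates participants 1:1 to DAM or NAM acupuncture, and the Discussion describes NAM as a placebo control. Section 2.8 sets out the comparison between arms: "Analysis of covariance will be performed to compare the results after acupuncture and during follow-up between the groups". The same section plans paired t-tests or Wilcoxon signed-rank tests, but only for change within a group.

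**The concern.** A paired-means test asks whether scores move from baseline in the same patients. The randomised question is whether they move more under DAM than under NAM. The two differ in two ways:

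- **Effect.** The between-group effect is the DAM change minus the NAM change, so any improvement in the control arm reduces it.
- **Variance.** With n per arm, the difference between two independent mean changes has twice the variance of one mean change.

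Both make the between-group test weaker than the paired test for the same before-after change, unless the control arm worsens or covariate adjustment recovers enough precision. No other part of the article gives a power for the comparison between groups. If 0.95 is taken as that power, a null DAM-NAM result would look more conclusive than the design may warrant.

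**Working it through.** **Inputs from the article.** 78 evaluable patients, power 0.95, significance level 5%, 15% dropout and 45 per group (section 2.4); 1:1 allocation (section 2.3); ANCOVA between groups (section 2.8).

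**Assumptions, since the article gives no figure.** Two-sided testing. The number 78 is read either as 39 patients per group or as 78 pairs in one calculation. Baseline-outcome correlation rho is 0.3 to 0.7, with equal SDs at baseline and week 8.

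**Step 1: the plan's own figure.** N = 78 cannot be reproduced without an effect and SD. It can be inverted. Paired power follows a noncentral t with n - 1 degrees of freedom and noncentrality dz × √n, where dz is mean change divided by SD of change. Setting power to 0.95:

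- n = 39: dz = 0.592 (noncentrality 0.592 × √39 = 3.70)
- n = 78: dz = 0.413 (noncentrality 0.413 × √78 = 3.65)

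**Step 2: the same effect between two groups.** Let the between-group difference in change be f × dz, with f = 1 if NAM does not change and f = 0.5 if NAM achieves half the DAM change. The two-sample noncentrality is f × dz × √(n/2), with n per arm. At n = 39 and f = 1 it is 0.592 × √19.5 = 2.61, or 0.413 × √19.5 = 1.82. For ANCOVA the difference is divided by √((1 + rho)/2), because the SD here is that of change.

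| 38-39 evaluable per arm, two-sided 5% | 78 = 39 per group (dz 0.592) | 78 = pairs (dz 0.413) |
|---|---|---|
| Two-sample, no NAM change | 0.72-0.73 | 0.43-0.44 |
| ANCOVA, rho 0.7 to 0.3, no NAM change | 0.79-0.89 | 0.49-0.61 |
| Two-sample, NAM achieves half | 0.25 | about 0.14 |
| ANCOVA, rho 0.7 to 0.3, NAM achieves half | 0.28-0.36 | 0.16-0.20 |

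If testing were one-sided throughout, the implied dz would be 0.536 or 0.376, and two-sample power at 39 per arm with no NAM change would be 0.76 or 0.50.

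**Step 3: what would give 0.95.** By a two-sample test with 39 per arm, the true difference must be about 0.83 SD. That is 0.827/0.592 = 1.40 times the implied effect on the 39-per-group reading. On the same reading, ANCOVA reaches about 0.95 if rho is near zero and NAM does not change; at rho = 0.1 it is 0.93-0.94.

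**Step 4: dropout.** 78/0.85 = 91.8, so 92. The stated 90 agrees with 78 × 1.15 = 89.7. Enrolling 90 leaves 90 × 0.85 = 76.5, about 76 evaluable or 38 per arm.

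**The case against.** The wording on differences in the placebo and acupuncture groups may mean that a contrast of changes was intended. Section 2.8 does plan within-group paired tests, so the calculation matches one planned analysis. The inputs sit in a cited study, and a condensed article need not repeat them. The illustrative powers rest on an effect inverted from N and power, not on anything measured.

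Much of this stands. The missing inputs are not a defect in themselves, and the figures above are conditional. It does not cure the mismatch: unmatched parallel groups cannot be compared by a paired test, and the within-group tests do not use the randomisation. If a contrast of changes was intended, the named test is wrong for it.

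A reader might infer three stronger things that the document does not support:

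- **That no reading gives 0.95, or that the trial is demonstrably underpowered.** Power of 0.95 is reachable with a near-zero correlation and no NAM change, with a true difference of about 0.83 SD, or if NAM worsens by about 40% of the DAM improvement. The article justifies none of these, but it excludes none either.
- **That the Borg figure of 0.97 is also a paired result.** Section 2.4 names no test for it. For the same reason it cannot be used to support the VAS figure.
- **That the dropout step is a material error.** The gap is two patients and costs about 0.01 in power, and the article does not state the formula it used.

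**Conclusion.** The point holds as a mismatch between the test used for sizing and the comparison the trial is randomised to make. The stated 0.95 belongs to a before-after test and is not shown for DAM versus NAM. That conclusion rests on the text alone and is firm.

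The size of any shortfall is not known. Under the stated assumptions and with no NAM change, power runs from about 0.43 (two-sample, 78 pairs) to 0.89 (ANCOVA at rho = 0.3, 39 per group), and it is much lower if NAM achieves half the change. No change under NAM is a favourable assumption: section 2.5 describes NAM as needling 2.0 cun from the DAM points over the same 8 weeks. The correction matters because section 2.4 is the article's only quantitative justification of the trial's size.

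**What to change.** Keep 90 participants and stop presenting 0.95 as the power of the trial. Replace the paired calculation with a two-sample or ANCOVA statement for the between-group VAS difference, giving the assumed difference, SD, correlation and sidedness.

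State what 90 delivers. With 15% dropout, about 76 evaluable (38 per arm) detect a difference of 0.65, 0.75 or 0.84 SD at 80%, 90% or 95% power by a two-sample test, two-sided 5%. Under ANCOVA, say which SD is meant:

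- SD of the post-treatment score: multiply by √(1 - rho²).
- SD of change: multiply by √((1 + rho)/2).

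The two multipliers agree at rho = 0.5 (0.87, so 0.65 becomes 0.56) but not elsewhere: at rho = 0.7 they are 0.71 and 0.92.

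For the Borg figure of 0.97, state which test it refers to, and do not present it as between-group power unless it is. As a minor correction, 15% dropout on 78 gives 92, not 90; stating the power at 76 evaluable settles this.

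The cost is wording in the sample-size section and a less favourable stated power. No extra patients are needed.

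### Section 2.4: 78 patients after 15% dropout needs 46 per group, not 45, and the section uses two dropout rates for the same visits (minor)

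*Protocol article*

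**What the plan says.** Section 2.4 of the protocol article gives two sample size calculations.

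- **VAS.** The calculation, made with a paired-means procedure, finds that "a total of 78 patients with stable COPD should be included in the study to achieve a statistical power of 0.95" at a 5% significance level. Dropout is then added: "Assuming a dropout rate of 15% established the necessity of a sample size of 45 participants per group".
- **Borg scale.** The calculation finds that "a total of 16 patients with stable COPD should be included in the study to achieve a statistical power of 0.97", also at 5%. The allowance for loss is different: "Assuming a dropout rate of 20%, a sample size of 10 participants per group is required".

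The section ends by saying that a multicentre trial needs a larger sample and that 90 is reasonable. It prints no inflation formula, gives no reason for the two dropout rates, and does not say whether the 5% is one-sided or two-sided.

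**The concern.** Two things in the section do not fit together.

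First, the VAS line prints all the inputs of a dropout adjustment (78 needed, 15% lost) together with its result (45 per group), and the result is too small for the inputs. The VAS calculation sets the size of the trial, so the stated power of 0.95 is attached to a number of patients that 90 enrolled would not leave at the stated loss.

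Second, one trial is given two dropout rates. Table 1 puts the Borg scale and the VAS in one row, at baseline and 8 weeks. Section 2.6.1 has both scored within a minute of the end of the same walking test. Section 2.2.4 withdraws patients from the study, not from one scale. A patient lost before week 8 therefore loses both scores, and nothing in the article explains why one scale should lose 15% and the other 20%.

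What is at stake is whether the published sample size statement agrees with its own inputs. The design does not depend on it.

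**Working it through.** **Inputs, all from section 2.4 (1:1 allocation from section 2.3).** VAS: 78 in total, so 39 per group; power 0.95; alpha 5%; dropout 15%; stated result 45 per group. Borg: 16 in total, so 8 per group; dropout 20%; stated result 10 per group. Final enrolment: 90. Because dropout is added afterwards, 78 and 16 are read as the numbers needed after losses.

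**1. Reproducing the stated figures.**

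| Calculation | n × (1 + d) | n/(1 − d) | Stated |
|---|---|---|---|
| VAS, per group | 39 × 1.15 = 44.85 → 45 | 39/0.85 = 45.88 → 46 | 45 |
| VAS, total | 78 × 1.15 = 89.7 → 90 | 78/0.85 = 91.76 → 92 | 90 (2 × 45) |
| Borg, per group | 8 × 1.2 = 9.6 → 10 | 8/0.80 = 10 | 10 |

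The VAS line matches the multiplication exactly and misses the division by one patient per group. The Borg line fits both formulas, so it does not show which one was used.

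**2. What 90 enrolled delivers.**

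- At 15% loss: 90 × 0.85 = 76.5, about 76 (38 per group).
- Loss at which 78 is just kept: 1 − 78/90 = 13.3%.
- Sensitivity case, 20% loss: 90 × 0.80 = 72 (36 per group). Keeping 78 at that rate would need 78/0.80 = 97.5, so 98 (49 per group).
- Borg at 20% loss: 72 against 16 needed, which is 4.5 times the target.

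**3. Effect on power.** The article gives no effect size or standard deviation, so the 78 cannot be rebuilt. The check takes power 0.95 at 78 as given and scales it with √n. For a two-sided 5% test:

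power(n) = Φ[(1.960 + 1.645) × √(n/78) − 1.960]

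- n = 76: 3.605 × √(76/78) − 1.960 = 1.60, so power is about 0.945.
- n = 72: 3.605 × √(72/78) − 1.960 = 1.50, so power is about 0.934.

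Noncentral t calculations, calibrated to 0.95 at the planned number, give about 0.945 and 0.933. This holds for a two-sample test with 39 per group and for a paired test with 78 or with 39 pairs. A one-sided 5% test gives about 0.945 and 0.935 by the normal approximation. The loss is therefore about 0.5 points at 76 and about 1.7 points at 72, whichever form of test is assumed.

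**4. Whether the closing sentences add a margin.** They do not: 90 is 2 × 45, the number already derived for the VAS.

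**The case against.** The strongest case on the other side is that this is immaterial. The gap is two patients in 92, one per group, and costs about half a point of power. The 78 comes from a paired-means calculation whose inputs are not shown, so a shortfall of 1.5 patients against it says little about the trial's real power. The section also ends in a judgement that 90 is reasonable, not in an exact derivation. All of this stands on size, and it is why the point is minor. It does not make the printed statement correct, because 45 is presented as what 15% dropout requires.

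Three stronger readings are tempting, and the article does not support them.

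- **That the plan expects only 72 evaluable patients for the VAS.** It attaches 15% to the VAS and 20% to the Borg scale. Putting the Borg rate on the VAS target is the reader's combination, useful only as a sensitivity case. Read as written, 20% loss leaves the Borg calculation far more patients than it needs.
- **That the target was certainly multiplied by 1.15.** The match is exact but remains an inference, since no formula is printed. The shortfall does not depend on how 45 was reached.
- **That between-group power can be recomputed here.** That needs an effect size and a standard deviation, which the article does not give.

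**Conclusion.** The point holds as a minor error of arithmetic and consistency. On the section's own inputs, 15% dropout requires 46 per group where it states 45, and the two dropout rates conflict without explanation.

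The power figures in the working are relative to the plan's own 0.95 at 78. They rest on that figure being right, which cannot be checked from the article, and on power changing with √n. A reader might infer that the trial is materially underpowered because of the dropout step. It is not: even the sensitivity case costs less than two points. Whether the paired-means calculation suits a comparison of two groups is a separate question that this check does not settle.

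**What to change.** Keep 90 and correct section 2.4:

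1. State one dropout rate for both scales, or give the reason for two.
2. Inflate with n/(1 − d) and show the formula.
3. Then state one of the following:
   - 90 enrolled yields about 76 evaluable patients at 15% loss (72 if 20% is the chosen rate), with the slightly lower power of about 0.945 (or 0.933) on the plan's own basis; or
   - 78 evaluable patients assumes a loss of at most 13.3%.

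The cost is one or two sentences and a slightly less favourable figure. No extra patients are needed, and allocation and analysis do not change.
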